## 3.4 Study sites:

The trial will be conducted at the three SMART2D participating sites in Uganda, South Africa, and Sweden.

### 3.4.1 Uganda:

In Uganda, the trial will be conducted within the two districts of Iganga and Mayuge that host the Iganga-Mayuge Health & Demographic Surveillance Site (IMHDSS). The two districts are adjacent to each other and are located in eastern Uganda approximately 120 kilometers east of Kampala along the Kampala-Kenya Highway.

Briefly, Uganda implements a level based health care system. Health Centre level I (HC I) is the lowest level of health care serving at village level to approximately 1,000 people, and has no physical structure but is a team of community health workers (CHW). Health Centre level II (HC II) is at parish level serving approximately 5,000 people. It is headed by an enrolled nurse and has approximately 3 established staff. HC II implements the “minimum activity package” including treatment of common diseases (malaria, diarrhea, skin infections, etc), integrated preventive outreaches, immunization, antenatal care and referral. It is therefore possible to provide general health education on diabetes and non-communicable diseases at this level as well as basic messages on diet, physical activity and risky habits like smoking and harmful use of alcohol. Health Centre level II (HC III) is an intermediate referral level serving about 20,000 people at sub-county level, with additional services including normal deliveries, limited in-patient care and TB treatment. It is headed by a Clinical Officer and has a laboratory that conducts basic tests (malaria, urine, blood sugar and TB). At this level, it is possible in theory but not in practice to provide blood sugar tests for individuals with proximal risk factors and refer them for follow-up care. Health Centre level IV (HC IV) is mini-hospital referral unit serving about 100,000 people in a zone called a Health Sub-district, usually covering a county. They are headed by a medical officer and have nursing officers with diverse skills. HC IVs are supposed to provide comprehensive referral services as well as support to the lower health units in their catchment zone (county). At this level, it is possible to provide pragmatic follow-up programs for high risk groups identified through targeted screening and to coordinate and NCD prevention program for this health service zone. HC V is a district hospital, HC VI regional hospital, whereas HC VII the National Referral Hospital.

***Uganda health facilities to participate in the trial***

Only government owned public health facilities at level III to level V in Iganga and Mayuge Districts will participate in the trial. There are 4 HC IV and 19 HC III. The four HC IVs will all participate in the study, whereas 5 of the 19 HC III’s were selected to participate in the study, two from Mayuge District and 3 from Iganga District. The HC III facilities were selected such that they are reasonably far apart from each other, allowing for sufficient buffer zones between all participating health facilities to minimize chances of contamination between the trial arms. Table 9 gives the list of the selected health facilities, whereas Figure 9 shows the geographical location of the selected health facilities within the study area.

Table 9: Health facilities selected to participate in the trial

| **#** | **Name** | **Level** | **Sub-county** | **County** | **District** |
| --- | --- | --- | --- | --- | --- |
| **Iganga District** | | | | | |
| 1 | Lubira HC | III | Buyanga | Bugweri | Iganga |
| 2 | Busesa HC | IV | Ibalanku | Bugweri | Iganga |
| 3 | Bugono HC | IV | Nabitende | Kigulu North | Iganga |
| 4 | Namungalwe HC | III | Namungalwe | Kigulu North | Iganga |
| 5 | Busowobi HC | III | Nakigo | Kigulu South | Iganga |
| **Mayuge District** | | | | | |
| 6 | Kigandalo HC | IV | Kigandalo | Bunya East | Mayuge |
| 7 | Kityerera HC | IV | Kityerera | Bunya South | Mayuge |
| 8 | Baitambogwe HC | III | Baitambogwe | Bunya West | Mayuge |
| 9 | Mayuge HC | III | Mayuge Town Council | Bunya West | Mayuge |

Figure 9: Location of health facilities in Uganda selected to participate in the trial

[figure not shown]

### 3.4.2 South Africa

In South Africa, the trial site will be conducted at Khayelitsha. According to the census data (2011), there are about 391 749 people living in in this urban township. About 36% of those aged 20 years and older have completed Grade 12 or higher and 38% of the labor force (aged 15 to 64) is unemployed. In addition only 45% of the population live in formal dwelling (Census, 2011).

The health care system is organized in three levels namely primary health care (clinics and community care centers), secondary (regional hospitals) and tertiary (tertiary hospitals) level care. Chronic care services are offered at the primary level care and there is a hierarchical referral systems where problem cases are referred to secondary level care. At primary level care there are also Community Based Services (CBS) are provided by Non-profit Organizations (NPOs)/ non-government organizations (NGOs), subsidized by the Provincial Government. The Western Cape Chronic Disease Policy has set up community-based support groups via local NPOs/NGOs - with input from the Community Health Centers. The implementation of support groups is seen as a way to improve adherence and increase self-management amongst patients. These community support groups are run by community health workers.

***South Africal health facilities to participate in the trial***

In South Africa, chronic care is offered at primary health care (PHC) facilities. In Khayelitsha PHC services are provided at 14 facilities but only 7 offer chronic care services (Table 10). These facilities are governed by 2 administrative authorities. Governed by the Provincial Government and Local Municipality (City of Cape Town)

Table 10: Facilities offering services to patients with chronic conditions

| **Name of Facility** | **Area** | **Administrative Authority** |
| --- | --- | --- |
| Khayelitsha Day Hospital/CHC | Site B | Provincial Department |
| Nolungile Day Hospital/CHC | Site C | Provincial Department |
| Michael Mapongwana Day Hospital/CHC | Harare | Provincial Department |
| Luvuyo Clinic | Makhaza | Local Authority |
| Kuyasa Clinic | Kuyasa | Local Authority |
| Matthew Goniwe Clinic | Makhaza | Local Authority |
| Town 2 Clinic | Town 2 | Local Authority |

Figure 10 shows the distribution of facilities offering services for chronic conditions that will participate in the study.

Figure 10: Location of health facilities in Khayelitsha, Cape Town, selected to participate in the trial

For the SMART2D intervention, only health facilities attached to a non-governmental organization utilizing CHWs will participate in the trial.

The SMART2D study sites will be 2 or four neighborhoods based on the facility that will be selected.

### 3.4.3 Sweden:

Migration has shaped Sweden over a long time. In the late nineteenth century 1.5 million Swedes migrated to America mainly due to poverty and to religious and political repression. During 1887 as many as 50,000 Swedes emigrated to the Americas. This record was only broken in 2011 when 51,000 Swedes emigrated to other countries in Europe, America and China; however the reasons were different (and the total population of Sweden about twice as large).

Currently immigration to Sweden involves two parallel processes: labor immigration and refugee immigration. An increase in political instability around the world has led to large groups of people fleeing their home countries, and immigration to Sweden has grown significantly. During 2014, the total population of Sweden increased by around 100,000 mainly due to refugees from Syria, Iraq, Afghanistan, Eritrea and Somalia seeking asylum in Sweden. Political unrest in Latin America and the Balkans in the 1970’s and 1980’s led to immigration waves from these areas. About 21 percent of the population in Stockholm is born outside Sweden or have parents not born in Sweden (16 percent in the nation).

Stockholm is a capital city characterized by a strong urbanization and with more than two million inhabitants– out of almost ten living in Sweden. The popularity of Stockholm is positive even though it brings challenges such as a competitive housing & job markets, pressure on schools and healthcare, and on traffic. Segregation and the development of an increasing number of neighborhoods with high immigrant density have emerged as a political issue during the last 20 years. These neighborhoods are composed of residents of many nationalities, in some cases from more than 100 countries. There are no neighborhoods where one single ethnic group comprises more than 10 percent of the population.

The SMART2D study sites will be in two or four such neighborhoods yet to be selected. The neighborhoods are geographically located in the suburbs of Stockholm in areas built during the 1960s as part of a “Million Homes Programme” that provided a million apartments over a short period of time. Rental housing dominates in these areas in addition to condominiums (*bostadsrätt*). The neighborhoods are considered to be socially vulnerable with low income levels and high unemployment rates. The mobility in these neighborhoods is higher than in areas where residents are mainly born in Sweden. The dynamics of mobility within segregated areas is a relatively new field of research in Sweden and findings from one recent study suggests that residents born in Sweden are less inclined than most migrant groups to move into migrant dense areas.

Healthcare in Sweden is publicly financed and the primary health care is the point of entry for persons seeking preventive or curative services. The primary healthcare centers provide the main part of the services for persons with diabetes and other chronic conditions. Diabetes rates are increasing in Stockholm. The share of persons diagnosed with diabetes was 4.6% in 2010 compared to 2.8% in 1990. Increasing overweight and obesity problems in the population are likely the main reasons for this trend. Socially disadvantaged neighborhoods have higher rates of disease, in particular diabetes. Women in areas with poor socioeconomic conditions have two to three times more often diabetes than women in the rest of Stockholm County.

***Sweden health facilities to participate in the trial:***

In Sweden, a health-centre and its catchment area (defined as the areas represented by the zip-code numbers of the patients currently registered in the health centre) will be designated as a cluster. The 4D project, jointly managed by Karolinska Institutet and the Stockholm County Council looks at four disease conditions within Stockholm County, of which diabetes is one. The Swedish arm of SMART2D is collaborating with the ‘diabetes’ part of the 4D project in Stockholm. As the 4D project has already developed a working collaboration with four primary care centres in Stockholm area to develop and implement quality control measures and to understand the healthcare-patient dynamics for diabetes, SMART2D will also be working in these centres. The municipalities being served by these four primary healthcare centres and their proportion of immigrant populations and the CNI index is given in Table 11 below. Figure 11 shows the geographical locations of the health centers selected to participate in the study.

Table 11: Municipalities considered for participation in the trial

| **#** | **Municipalities** | **% of migrants** | **CNI *** |
| --- | --- | --- | --- |
| 1 | Järfälla (Jakobsberg) | 36% | 1.42 |
| 2 | Hässelby-Vällinby (Hässelby) | 36% | 1.70 |
| 3 | Spånga-Tensta (Tensta) | >75% | 2.54 |
| 4 | Spånga-Tensta (Rinkeby) | >75% | 2.44 |

*Care Need Index - a social deprivation index

There are currently diabetes-focused interventions underway in Flemingsberg and therefore will have to be excluded. Of the remaining four, Tensta and Rinkeby are migrant-dense areas (>75%) with more mobile and socio-economically disadvantaged populations. Jakobsberg and Hässelby on the other hand have comparable proportion of immigrants (36%), who are more stable and socio-economically more advanced.

Figure 11: Location of health facilities in Stockholm Sweden, selected to participate in the trial

[figure not shown]

## 3.5 Study Participants:

Participants will be residents within the identified catchments areas at each of the study sites as described above. Eligible subjects will be:

1. current residents who have resided in their respective communities for at least 6 months prior to enrollment into the study,
2. aged 30 – 75 years,
3. currently not known to be pregnant
4. have no plans of migrating out of the study area over the next 12 months from the date of enrollment into the study,
5. able to provide written informed consent,
6. agree to allow home visits and follow-up contacts as part of participating in the trial,
7. no previous diagnosis with diabetes, or diagnosis of diabetes of no longer than 12 months prior to being screened for enrollment into the study
8. have a positive confirmatory test of pre-diabetes or diabetes

## 3.6 Recruitment and enrollment of participants

Prior to initiation of the trial, the pre-identified health facility clusters will be randomized either to the facility only, or to the facility plus the community arm al the three country sites; and additional to the current practice arm in Uganda. Each site will screen subjects in their study population to identify potential trial participants, using different algorithms as described below.

### 3.6.1 Uganda

***Community sensitization:***

In Uganda, engagement of the community will begin with sensitization of the political and health service delivery leadership in the two districts of Iganga and Mayuge. A number of meetings will be conducted in which the study team will provide the necessary information about the planned study to the district health and political leaders in the two districts. The leaders to be targeted will include the District Health Officers of the two districts, local council chairpersons, and the in-charges of the health facilities to participate in the study. Study investigators will make presentations to the community leaders to explain the objectives of the study, the participant recruitment process, procedures to be conducted on enrolled participants, the benefits, and the risks of participating in the study. The leaders will be allowed to ask questions and answers provided. Subsequently, radio talk shows on the local radio station (Busoga FM) will be conducted to provide information about the planned study to the wider community in the two districts.

***Recruitment:***

Once the sensitization activities are completed, trained Field Research Assistants (FRA) will approach households within each of the specified cluster communities, explaining the study to household members, and seeking consent to participate in screening for the trial. The FRA will seek a written pre-eligibility screening informed consent from adult members of the household. The FRA will then administer a short screening form to consenting adults to identify potential trial participants. In this first stage of screening, potential eligible household members would need to meet the following criterion:

1. current resident that have resided in their respective communities for at least 6 months prior to the date of screening
2. have no plans of migrating out of the study area over the next 12 months from the date of enrollment into the study,
3. aged 30 – 75 years,
4. currently not known to be pregnant
5. no previous diagnosis with diabetes, or diagnosis of diabetes of no longer than 12 months prior to the date of screening

The FRA will arrange an appointment with household members that meet the preceding criteria to return early morning on an agreed date, for a fasting plasma glucose (FPG) test. The FRA will return to the household on the agreed morning and conduct the FPG test usig an AccuCheck glucometer.

The FRA will arrange for a second FPG test for subjects with the first (Test 1) FPG results of at least 6.1 mmol/L (see Figure 3.7). Potentially eligible household members will those with a second (Test 2) FPG test result of at least 6.1 mmol/L, and will be referred to the respective cluster health facility for a confirmatory eligibility FPG test. The subjects will be given a referral note, and advised to report to the health facility within seven days, after an overnight fast on the day they report, with no exercise or smoking.

On presentation to their respective health facility with the referral note, a third FPG test will be conducted to confirm eligibility. Subjects will be classified as: a) normal if two of their FPG tests are less than 6.1 mmol/L, b) pre-diabetes if two of their FPG tests is between 6.1 and 6.9 mmol/L, and, c) diabetic if two of their FPG test results are greater than 6.9 mmol/L. Figure 12 and Table 12 summarizes the decision guide to identify eligible subjects in Uganda, as far as their FPG levels are concerned.

Figure 12: Algorithm for sequence of screening tests for Uganda

[figure not shown]

Table 12: Decision guide to enroll for Uganda

| **Test 1***  **(PoC FPG at home)** | **Test 2***  **(PoC FPG at home)** | **Test 3***  **(PoC FPG at health facility)** | **Outcome** |
| --- | --- | --- | --- |
| FPG = 6.1-6.9 | FPG ≥ 7.0 | FPG= 6.1-6.9 | Pre-D: RECRUIT |
|  |  | FPG ≥ 7.0 | T2D: RECRUIT |
|  | FPG= 6.1-6.9 | n/a | Pre-D: RECRUIT |
|  | FPG< 6.1 | Not eligible | DO NOT RECRUIT |
| FPG ≥ 7.0 | FPG > 7.0 | n/a | T2D: RECRUIT |
|  | FPG= 6.1-6.9 | FPG= 6.1-6.9 | Pre-D: RECRUIT |
|  |  | FPG ≥ 7.0 | T2D: RECRUIT |
|  | FPG < 6.1 | Not eligible | DO NOT RECRUIT |

*FPG values based on WHO recommendation[WHO 2006]

Following eligibility confirmation on the day they report for their FPG Test 3, an “Eligibility Confirmation Form” will be administered, and written informed consent obtained from the subject prior to enrollment into the trial. Briefly, a study staff at the health facility will provide information on the study objectives, study procedures, benefits from participating, risks of participating, and confidentiality issues will be emphasized using a written consent form document. Importantly, even while participating in the trial, participants will continue receiving standard medical care as needed, and as available at the health facility. Administration of any study procedures will only happen after the eligible subjects have consented to participate in the study. After a subject has consented to participate in the study, the subject will be enrolled with assignment of a unique study number and baseline evaluation conducted.

### 3.6.2 South Africa

**3.6.1.** **Community sensitization**

Community engagement will be implemented by sensitizing key stakeholders, incl. NGOs and health service providers within the Khayelitsha Eastern Sub-Structure (KESS). A series of meetings will be conducted in which the study team will provide information about the planned study to the stakeholders in the sub-Structure, including the KESS Director, local NGOs, and the managers of the selected study facilities. Study investigators will also conduct a community awareness raising campaign in partnership with the local branch of a National NGO to drive participant recruitment. The venue will be a central location which draws large numbers of visitors, such as a shopping mall located in close proximity to the study facilities.

Recruitment drivers will screen consenting adults to identify potential trial participants. They will conduct a random plasma glucose (RPG) test and refer eligible participants in line with the diagnostic criteria outlined in the Practical Approach to Care Kit (PACK) guidelines for primary care to the health facility to test for fasting plasma glucose (FPG) (Figure 3.2). Patients with an RPG ≥ 6.1 mmol/L will be advised to visit their health facility within a week, after an overnight fast on the day they report with no exercise or smoking.

**3.6.2.** **Facility recruitment**

Recruitment will take place at the two selected facilities. Persons presenting at the facilities who are either diagnosed with T2DM, or present with NCDs risk factors, including obesity, high blood pressure and/or impaired glucose tolerance, will be invited to participate in the trial. They will be recruited when visiting the facility for routine clinical care or upon referral from the community as per the above outlined protocol. Subjects will be classified as diabetic if two consecutive FPG tests > 6.9 mmol/L and as pre-diabetic if two consecutive FPG tests are between 6.1-6.9 mmol/L. A third FPG test may be needed to validate different test results (Figure 13 and Table 13).

Following eligibility confirmation, an ‘Eligibility Confirmation Form’ will be administered and written informed consent sought from the subject prior to study enrollment. Briefly, the study manager at the health facility will provide information on SMART2D study objectives, procedures, benefits and risks of participating, as well as confidentiality issues. Participants will receive a consent form and continue to receive standard medical care as needed, and as available at the health facility. Administration of any study procedures will only happen after eligible subjects have consented to participate in the study, upon which they will be enrolled and given a unique study number.

*Figure 13 Algorithm for sequence of screening tests for South Africa*

[figure not shown]

**FPG (TEST 2)**

**FPG (TEST 2)**

*Table 13: Decision guide to enroll for South Africa*

| **RPG**  **(mmol/L)** | **Test 1 (FPG)**  **(mmol/L)*** | **Test 2 (FPG)**  **(mmol/L)*** | **Outcome** |
| --- | --- | --- | --- |
| RPG ≥ 6.1 | FPG > 6.9 | FPG > 6.9 | T2DM (RECRUIT) |
|  |  | FPG= 6.1-6.9 | AT RISK (RECRUIT) |
|  | FPG = 6.1-6.9 | FPG= 6.1-6.9 | AT RISK (RECRUIT) |
|  |  | FPG < 6.1 | NOT ELIGIBLE |

*FPG values based on WHO recommendation [WHO 2006]

### 3.6.3 Sweden

In Sweden, since the suburbs chosen varied in terms of the composition of immigrant groups and the overall socio-economic status, the catchment area of each of the participating health centres were divided into zones using postal codes. These zones were randomly allocated to primary care versus integrated care, taking care to prevent contamination and spillover. Participants are recruited to the trial through community screening. The research team with input from health centres and municipalities have identified opportunities and spaces in the community to carry out screening activities. Both research staff as well as outreach workers from the municipalities are involved in mobilizing community members and inviting them to participate in the screening, by: 1) facilitating access to the target population through local NGOs, immigrant associations, religious bodies, such as churches and mosques, and cafes or other ventures owned by immigrant groups; 2) identifying and facilitating access to spaces to set up the screening activities such as shopping malls, local library, municipality hall or other public spaces such as swimming halls.

Community screening activities are carried out by the research team on weekdays and weekends using a combination of FINDRISC [J. Lindström et al. 2003], and hemoglobin A1c (HbA1c) test (both point-of-care and lab-based) using a recruitment algorithm summarized in Figure 14 and Table 14. All individuals with HbA1c values in the diabetes or pre-diabetes range are referred to the health centres to be registered and enrolled into the primary care only arm, or the integrated care arm as the case may be.

Figure 14: Algorithm for sequence of screening tests for Sweden

[figure not shown]

Table 14: Decision guide to enroll for Sweden

| **Test 1 (POC HbA1c)*** | **Test 2 (Lab HbA1c)*** | **Outcome** |
| --- | --- | --- |
| HbA1c = 42-47 | HbA1c = 42-47 | **Pre-D: RECRUIT** |
|  | HbA1c ≥ 48 | **T2D: RECRUIT** |
|  | HbA1c < 42 | NOT ELIGIBLE |
| HbA1c ≥ 48 | HbA1c ≥ 48 | **T2D: RECRUIT** |
|  | HbA1c = 42-47 | **Pre-D: RECRUIT** |

*HbA1c values based on WHO and ADA recommendation[WHO 2011; ADA 2016]

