# 3.0 DESIGN AND METHODS

## 3.1 Study Design:

A stratified cluster-randomized trial design will be used. At each of the study sites, the clusters will be the catchment areas of participating health facilities. The health facility clusters will be randomized to either the facility alone arm, or the facility + community arm. Thus each health facility to participate in the trial, together with the community in its catchment area will be the units of randomization. Although the clusters will be the units of randomization, the enrolled individual participants will be the primary study units of measurement.

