$\mu_{0}$ = mean value of outcome variable (HbA1c) at month 12 in the comparison (control) arm

$\left( \mu_{0}-\mu_{1} \right)$ = minimum effect size to be detected

[figure not shown]

[figure not shown]

The necessary sample size for a cluster randomized trial depends on the variation in the intervention effects between the arms, and the clustering due to trial arm allocation (which reduces the variance of the difference between the arms), and the correlation between the repeated observations in each participant. Given that we have a fixed number of health facilities (clusters), to adjust for clustering we used a formula for fixed number of clusters and fixed number of participants within clusters as described in Hemming et al (2011) page 19 [Hemming et al. 2011].

$$Sample size per cluster=\frac{n_{i}*k*\left( 1-\rho\right)}{\left( k-n_{i}*\rho\right)}$$

where: $n_{i}$ = initial sample size

$k$ = number of clusters

= inter-cluster correlation

[figure not shown]

[figure not shown]

It is important to note that each site will be using different numbers of clusters; specifically Uganda will be working in 9 clusters, Sweden in 4 clusters, whereas South Africa will be working in 2 clusters. Thus different inter-cluster correlation (ICC) coefficient values are expected. We were unable to find published literature providing estimates for ICC coefficients for HbA1c among persons with pre-diabetes. We therefore explored various values of ICC coefficients for each site, and used values that provided the highest sample sizes to detect the desired effect size. For Uganda we used an ICC value of 0.200 to obtain a sample size of 112 participants, for South Africa we used an ICC value of 0.044 to obtain a sample size of 129, whereas for Sweden we used an ICC value of 0.06 to obtain a sample size of 79; all per study arm. For Sweden, there will be a further interest to compare the primary outcome of interest between immigrant participants of non-European origin versus immigrant participants of European origin. In order to allow for this sub-analysis, the sample size of 79 for Sweden was doubled to 158 to enable detection of the same effect size between immigrant participants of non-European origin versus immigrant participants of European origin.

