| **STEP 2** | **Answer the following ELIGIBILITY questions** | **No** | **Yes** |  |
| a) | Has the individual been a resident in the location of the interview for less than 6 months? | └──┘ | └──┘ | ELI_2a |
| b) | Is the individual less than 30 years, or older than 75 years of age | └──┘ | └──┘ | ELI_2b |
| c) | Has the individual indicated that he/she has plans of migrating out of the study area over the next 12 months? | └──┘ | └──┘ | ELI_2c |
| **For participants with pre-diabetes, SKIP to (e)** | | | | |
| d) | Was the individual diagnosed with diabetes longer than 12 months before being screened for the SMART2D intervention trial?  REDCAP: "FOR INTERVIEWERS: If the participant has pre-diabetes, mark the selection 'Participant has pre-diabetes'" | 0 = No  1 = Yes  2 = Participant has pre-diabetes | | ELI_2d |
| e) | If female, is the individual pregnant?  **If male, SKIP to (f)**  REDCAP: "FOR INTERVIEWERS: If the participant is male, mark the selection Participant is male" | 0 = No  1 = Yes  2 = Participant is male | | ELI_2e |
| f) | Has the individual been diagnosed with heart disease, stroke or peripheral vascular disease/serious mental disorders affecting cognitive functions? | └──┘ | └──┘ | ELI_2f |
| g) | Has any other individual in the same household been enrolled in this study? | └──┘ | └──┘ | ELI_2g |
| h) | Is the individual enrolled in any other study related to diabetes/ self-management | └──┘ | └──┘ | ELI_2h |
| 🡺 If all of the responses in STEP 2 are NO, the subject is ELIGIBLE to be recruited for the trial. If more than one individual in a household is found eligible, apply the KISH methodology (See Appendix 1). | | | | inst_eli_2 |

| **SECTION 2: IDENTIFICATION INFORMATION**  (Instruction: To be included in each set of participant questionnaires) | | | |
| --- | --- | --- | --- |
| **S.NO:** | **Questions** | **Response** | **Code** |
| A | Site Identification Number  UG/SA/SW | └──┘└──┘ | SI_ID |
| B | Cluster/facility Identification number  *Each site to assign numbers to each cluster (SA: 1-2, SW: 1-4, UG: 1-9)* | └──┘ | CL_ID |
| C | Trial arm identification code | 1= Facility only  2 = Facility + community └──┘  3 = No intervention (Uganda only) | TA_ID |
| D | Unique Participant ID number *(Assigned by study team in the field - assign a range of numbers to each cluster)* | └──┘└──┘└──┘ | PA_ID |
| E | To which diagnostic group is the participant recruited? | 1 = Diabetes  2 = Pre-diabetes └──┘ | DX_ID |

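### The protocol gives two incompatible units of randomisation for Sweden (postal-code zones or whole health centres), and its stated Swedish power is tied to neither

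*Protocol*

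**What the plan says.** **Zones.** Section 3.6.3 reports that "the catchment area of each of the participating health centres were divided into zones using postal codes", and that "These zones were randomly allocated to primary care versus integrated care, taking care to prevent contamination and spillover". The number of zones is not given, and neither is the number per centre or per arm.

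**Centres.** Section 3.1: "Thus each health facility to participate in the trial, together with the community in its catchment area will be the units of randomization". Section 3.6 repeats this for all three countries: "the pre-identified health facility clusters will be randomized either to the facility only, or to the facility plus the community arm". Section 3.4.3 says that a Swedish health centre with its zip-code catchment "will be designated as a cluster".

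**Sample size.** Section 3.10 counts facilities as clusters ("Given that we have a fixed number of health facilities (clusters") and puts Sweden at 4, in the text and in Tables 16(a) and 16(b).

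**Identifiers.** Section 2 of the data collection tools instructs: "Each site to assign numbers to each cluster (SA: 1-2, SW: 1-4, UG: 1-9". The study number in section 3.7 carries a facility/cluster code and an arm code. Neither place has a zone code.

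**Analysis.** Section 3.13.1 plans GEE for within-cluster correlation, and a mixed model with one random intercept and robust standard errors. It does not name the level of clustering and does not mention zones.

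**The concern.** In a cluster trial the allocated unit determines the design effect, the degrees of freedom and the identifier that must be collected. If zones inside a catchment were allocated, one centre may serve both arms. The arm comparison is then made at least partly within centres, and correlation within zones drives its error. If whole centres were allocated, Sweden has four units in two arms. These are different trials with different power, and the protocol describes both.

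Two things are at stake. The first is the stated 80% power for Sweden, which matters because section 3.10 intends each site to support its own comparison. The second is whether the data will identify the allocated unit. If several zones per arm exist within a centre and no zone code is kept, no later analysis plan can fully repair that.

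**Working it through.** **1. Reproduce the protocol's figures.** Inputs from section 3.10 and Tables 16(a) and 16(b): initial size n_i = 34 (pre-diabetes) and 58 (diabetes) per arm; k = 4 for Sweden; ICC ρ = 0.070 (Table 16(a)) and 0.020 (Table 16(b)); two-sided 5%, 80% power. Formula in section 3.10: n = n_i·k·(1−ρ)/(k − n_i·ρ).

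- Pre-diabetes: 34×4×0.93/(4 − 2.38) = 126.48/1.62 = 78.07, so 79. This matches. The ICC of 0.06 printed in the text gives 127.84/1.96 = 65.22, so 66, and does not match.
- Diabetes: 58×4×0.98/(4 − 1.16) = 227.36/2.84 = 80.06, so 81. This matches.

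**2. What k means in this formula.** Section 3.10 uses the result as a size per arm. Write n = n_i·[1 + (n/k − 1)ρ] and solve for n: the printed formula follows. Here n/k is the cluster size within an arm, so k is the number of clusters **per arm**. The Swedish 4 is a site total. The Ugandan figures (112, 128) and South African figures (129, 136) also reproduce with site totals of 9 and 2.

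**3. Does k = 4 per arm fit either account?** Four whole centres in two arms give 2 per arm, so no. Zones fit only if there are four per arm, for example one zone per arm in each of four centres. The protocol does not say so.

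**4. Range.** The zone count and a zone-level ICC are not given. I assume 2 to 12 clusters per arm and keep the protocol's n_i and ρ. Effective size n_e = n/[1 + (n/k − 1)ρ]. Power = Φ(√(n_e/n_i)×2.80 − 1.96), where 2.80 = 1.96 + 0.84.

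| Clusters per arm | Pre-diabetes: n needed | Power at 79 | Diabetes: n needed | Power at 81 |
|---|---|---|---|---|
| 2 | not attainable | 60% | 136 | 70% |
| 4 | 79 | 80% | 81 | 80% |
| 8 | 46 | 92% | 67 | 86% |
| 12 | 40 | 95% | 63 | 88% |

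Worked case, pre-diabetes, k = 2: n_e = 79/(1 + 38.5×0.07) = 79/3.695 = 21.4, and power = Φ(√(21.4/34)×2.80 − 1.96) ≈ 60%. The requirement is not attainable because k − n_i·ρ = 2 − 2.38 is negative.

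The text doubles the sizes to 158 and 162 for the origin sub-analysis. At k = 2 the doubled pre-diabetes size still has n_e = 158/(1 + 78×0.07) = 24.5, below 34. The doubled diabetes size does exceed the 136 needed.

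**5. Consequence for type I error if zones were allocated.** I used a null simulation with zones randomised in balance within 4 centres (all assumed: 158 participants, centre ICC 0.03, 2 to 6 zones per centre, 4,000 runs per setting).

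| Analysis | Zone ICC 0 | 0.02 | 0.06 |
|---|---|---|---|
| Centre intercept, model-based SE, zones ignored | about 5% | 6–10% | about 9–19% |
| Sandwich on 4 centres, normal reference | 18–19% | 18–19% | 18–19% |
| Zone means, centre as stratum, t reference | about 5% | about 5% | about 5% |

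The sandwich error is as large with no zone correlation as with an ICC of 0.06. With a small-sample scaling and a t reference on 3 degrees of freedom it returns to about 5%. Its fault is too few clusters.

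**The case against.** The strongest reply accepts that the wording conflicts but holds that little else is proved. Most of that stands.

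- **Standard errors.** A reader might infer that the planned Swedish standard errors use the wrong unit. Section 3.13.1 names no clustering level, the statistical analysis plan is not shown, and a sandwich variance on centres absorbs correlation among zones nested in them. The loss of type I error control through ignored zones applies to a model-based centre intercept, and that this would be the analysis is an inference.
- **Number of units.** A reader might infer that the allocated units cannot number four, or that k = 4 belongs to an abandoned design. The zone count is not stated. Section 3.4.3 still speaks of two or four neighbourhoods to be chosen, so two centres with two zones each would make four units in total. One zone per arm in each of four centres would make k = 4 right per arm.
- **Identifiers.** The form also records the arm. With exactly one zone per arm in each centre, the cluster and arm codes together identify the zone. With more zones they do not.
- **Contamination.** A reader might infer that spillover was overlooked. Section 3.6.3 says that it was considered when zones were allocated, and section 3.3.2.1 intends facility care to be standardised across arms.
- **Both arms in one centre.** This is likely under zoning but not stated, because section 3.6.3 does not say that allocation was balanced within centres.

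None of this reconciles section 3.6.3 with sections 3.1, 3.4.3 and 3.6.

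**Conclusion.** The contradiction is explicit and unresolved. The past tense of section 3.6.3 suggests that it records what was done, but the text does not settle which account is true.

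The stated Swedish 80% power has no defined basis, because k = 4 per arm is neither four whole centres nor a stated number of zones. On the protocol's own initial sizes and ICCs, power is about 60–95% (pre-diabetes, n = 79) and 70–88% (diabetes, n = 81) over an assumed 2 to 12 clusters per arm. It would be tempting to say that Sweden is underpowered. The documents do not support that, since many zones could give more power than claimed.

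These figures take 34 and 58 as given. Neither follows from the inputs stated beside it (about 11 and about 8,400 respectively), which is a separate matter. They use a normal approximation, so the results at 2 clusters per arm are optimistic. The type I error figures are conditional on zone allocation and on the assumed ICCs.

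**What to change.** State in section 3.1 which unit was randomised in Sweden, and bring sections 3.4.3, 3.6, 3.6.3 and 3.10, Tables 16(a) and 16(b), and the cluster field on the data form into line.

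**If zones:**
- Give the number of zones per centre and per arm.
- Add a separate zone identifier and keep the facility code.
- Analyse Sweden with zone as the cluster and a small-sample correction. Use health centre as a stratum if allocation was made within centres.
- Restate Swedish power with k as clusters per arm, over a range of zone ICCs.

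**If centres:** correct section 3.6.3 and restate Swedish power with 2 clusters per arm.

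In either case, define k in the same way for all three sites in Table 16. Changing Sweden alone would leave Uganda and South Africa on site totals.

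The cost is one data field at most, wording changes and a restated power figure. Zone membership should be recoverable from the participant's postal code if that is held at enrolment.
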